
#### Validation phase

Clinical software validation (Aim 2)

After screening of eligible patients written informed consent will be obtained from parents or caregivers.

Clinical screening will be performed as mandated by the Italian law. Pre-ductal (right arm) oxygen saturation and post-ductal (leg) oxygen saturation will be recorded. Physical examination will include femoral arterial pulse detection and face-to-face heart auscultation.

Clinical screening output threshold criteria is summarized in *Table 2*.

**Table 2 ztag103-T2:** Clinical screening output threshold criteria

	Positive screening	Negative screening
**Oxygen saturation**	<95% and/or arm-to-leg difference >5%	>95% and arm to leg difference < 5%
**Femoral arterial pulse**	Absent or reduced	Normal
**Heart auscultation**	Any divergence from normal cardiac auscultation	Normal I/II heart sound, venous hum, physiologic murmur

For this phase we will enrol patients using a block stratification for high SHD risk vs. low (standard) SHD risk status for each newborn.

Heart recordings will be acquired (15 s length) before comprehensive echocardiography by a trained research investigator. Age at recording and echocardiographic evaluation will be planned not before 7 days of post-natal life to allow completion of proper cardio-circulatory transition in the healthy newborns (i.e. ductal closure, pulmonary vascular remodelling, foramen ovale physiologic shunt).

The echocardiography will be performed according to current guidelines by expert paediatric cardiovascular imager blinded to clinical and digital screening results. Preliminary inter- and intra-observer variability between dedicated expert cardiovascular imagers among centres will be performed in small patient subset.

Pertinent anonymized demographics, cardiovascular status, and pertinent research variables will be stored in an encrypted, web-based, research-focused online software.

Digitally anonymized echocardiographic clips will be transferred to the Echocardiography Study Core Lab who will perform the final, formal reading of the exams dichotomizing patient population into normal and abnormal examination. Any potential conflict of interpretation will be solved with consensus and among all Units cardiac imagers.

Concordance/discordance pattern between patient-centred comparisons between digital and clinical screening results will be performed using the echocardiography as primary modality of outcome ascertainment (*Figure 1*). False positive will be defined healthy newborns receiving a ‘positive’ screening result using either the clinical (standard or face-to-face auscultation) or the digital approach. Similarly, false negative will be defined newborns with SHD receiving a ‘negative’ screening result using either the clinical (standard or face-to-face auscultation) or the digital approach.

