### Study procedure

#### Patient enrolment

For the derivation phase newborns without SHD will be enrolled at the time of discharge from Ob/Gyn programme and newborns with SHD will be enrolled at the time of cardiovascular examination. For the validation phase consecutive newborns will be enrolled at the time of discharge from Ob/Gyn unit.

*
Graphical abstract
* summarizes the study pipeline.

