Net classification improvement will be used as the major statistical analysis for Experimental Aim 2, using ‘standard of care’ screening modality as comparison group. Sensitivity, specificity, positive, and negative predictive values will be calculated, and likelihood ratio will be analysed. C-statistics will be used to compute diagnostic performance of newly validated algorithm. Bootstrapping will be used to generate confidence intervals.

For experimental design Aim 2, sample size calculation is being presented for sensitivity. Assuming a two-sided α of 0.05% and 90% power, and a disease prevalence of 1% consistent with prior newborn CHD screening studies, we based our calculation on methods for diagnostic test evaluation. Specifically, targeting a sensitivity of approximately 90% with a desired confidence interval width of ±10%, at least 19–20 cases of CHD are required. Given the low expected prevalence (1%), this corresponds to a total sample size of approximately 1900–2000 newborns. This approach is consistent with previously published recommendations for validation of diagnostic algorithms in low-prevalence settings.^34^ Accordingly, an independent validation cohort of approximately 1900 consecutively enrolled participants will be used.

Data will be reported as mean ± standard deviation, median (first and third quartile) or frequency (%). All tests were two-sided. A *P*-value <0.05 was considered significant. Standard statistical analysis will be performed using STATA® 17 h Release data analysis software (StataCorp LP, College Station, TX).

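### The validation cohort is enrolled in risk blocks but sized as about 1900 consecutive newborns at 1% prevalence; if the blocks enrich high-risk newborns, its predictive values reflect the block ratio

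*Protocol article*

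**What the plan says.** All references are to the Protocol article.

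- **Validation phase (Study procedure):** "For this phase we will enrol patients using a block stratification for high SHD risk vs. low (standard) SHD risk status for each newborn". No block ratio or stratum size is given.
- **Validation phase (Study population):** two groups are defined by pre-test probability. High-risk newborns have a suspicious foetal ultrasound or an indication for cardiology evaluation, which includes an abnormal neonatal screen. Low-risk newborns are consecutive neonates recruited specifically for the research. Only the low-risk group is described as close to population prevalence.
- **Patient enrolment:** "For the validation phase consecutive newborns will be enrolled at the time of discharge from Ob/Gyn unit".
- **Statistic plan, Aim 2, sample size:** "targeting a sensitivity of approximately 90% with a desired confidence interval width of ±10%, at least 19–20 cases of CHD are required", and then "Given the low expected prevalence (1%), this corresponds to a total sample size of approximately 1900–2000 newborns". The paragraph concludes that "an independent validation cohort of approximately 1900 consecutively enrolled participants will be used".
- **Statistic plan, Aim 2, analysis:** net classification improvement against standard-of-care screening is the main analysis. In addition, "Sensitivity, specificity, positive, and negative predictive values will be calculated, and likelihood ratio will be analysed", and C-statistics are planned. None of these is tied to a stratum.
- **Aim 3:** the target population is low-risk newborns only. Prevalence, sensitivity and specificity are model inputs.

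**The concern.** Recruiting in risk blocks and recruiting consecutively are different sampling schemes. If blocks set the share of high-risk newborns, the share of diseased newborns is set with it, and dividing the required cases by 1% no longer describes the cohort.

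Three things are then at stake.

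1. Predictive values taken straight from the cohort would carry the block ratio into figures that readers will take as screening performance.
2. Pooled sensitivity, specificity and C-statistic would depend on the mix if the classifier performs differently in newborns referred on suspicion and in those with no indication.
3. The main Aim 2 comparison would be affected because one route into the high-risk stratum is a result of the same kind as the comparator. Over-sampling screen-positive newborns changes the apparent sensitivity and specificity of clinical screening.

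**Working it through.** **1. The plan's own figure.** N = cases / prevalence: 19/0.01 = 1900 and 20/0.01 = 2000. This step reproduces exactly, so N rests on the whole cohort having 1% prevalence. (A separate matter, not relied on here: the 19–20 cases do not follow from 90% ± 10%. At two-sided 5%, 1.96² × 0.90 × 0.10 / 0.10² = 34.6, so 35 cases.)

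**2. Prevalence under block enrolment.** With high-risk share f and stratum prevalences p_H and p_L, cohort prevalence is π = f·p_H + (1 − f)·p_L. The article gives none of the three for the enrolled strata, so what follows is a range under assumptions.

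**3. Predictive values.** PPV = Se·π / [Se·π + (1 − Sp)(1 − π)]. Se 0.95 and Sp 0.90 are the Aim 1 targets, used for illustration.

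- π = 0.01: 0.0095 / (0.0095 + 0.0990) = 8.8%.
- π = 0.126: 0.1197 / (0.1197 + 0.0874) = 57.8%, about 58%. This π is an assumption: half the cohort high-risk, with SHD in 25% of high-risk and 0.26% of low-risk newborns. With 1% in the low-risk half instead, π = 0.130 and PPV is 58.7%.

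Range with p_L = 1% and p_H = 10% to 50% (all assumed), N = 1900:

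| High-risk share | Cohort prevalence | Cases in 1900 | of which low-risk | PPV |
|---|---|---|---|---|
| 10% | 1.9–5.9% | 36–112 | 17 | 16–37% |
| 25% | 3.3–13.3% | 62–252 | 14 | 24–59% |
| 50% | 5.5–25.5% | 105–485 | 9.5 | 36–76% |

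NPV moves less: 99.9% at π = 0.01 and 98.1% at π = 0.255. Total cases rise with enrichment, while low-risk cases fall below 19.

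**4. Pooled sensitivity and specificity.** These do not depend on prevalence itself. They move only if the strata differ. Assume Se 0.95 (high) and 0.80 (low), Sp 0.80 (high) and 0.92 (low), and prevalences 30% and 1%. Raising the high-risk share from 2% to 50% then moves pooled Se from 0.857 to 0.945 and pooled Sp from 0.918 to 0.870.

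**5. Net classification improvement.** Take the extreme case in which high-risk means screen-positive only. Assume clinical Se 0.75 and Sp 0.97 (inside the 70–80% and 95–99% quoted under Limitation), digital Se 0.95 and Sp 0.90 in both strata, and 1% population prevalence.

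- Screen-positive fraction: 0.75 × 0.01 + 0.03 × 0.99 = 0.0372.
- SHD among screen-positives: 0.0075/0.0372 = 20.2%. Among screen-negatives: 0.0025/0.9628 = 0.26%.
- At natural frequency: diseased component 0.95 − 0.75 = +0.20; non-diseased component 0.90 − 0.97 = −0.07.
- At 50% high-risk: apparent clinical Se = 0.2016/(0.2016 + 0.0026) = 0.987, and Sp = 0.9974/(0.9974 + 0.7984) = 0.555. The components become −0.04 and +0.34.

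Both signs reverse through sampling alone. Foetal-ultrasound and symptom referrals would dilute this.

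**The case against.** The strongest reply is that no sentence says high-risk newborns are over-sampled. Two sections call the cohort consecutive, and the block wording could mean no more than labelling each consecutive newborn by risk. At natural frequency the distortion disappears. This stands as a possibility, and it is why the point is conditional. It does not remove the conflict: the text never says that strata fill naturally, and it describes the low-risk group as a separately recruited stream.

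A reader might go further and infer that the cohort certainly will not be at 1% prevalence, or that its predictive values will apply to no screened population. The article does not support either reading, because it gives no ratio. Nor does it support the inference that pooled sensitivity must differ from low-risk sensitivity; that needs a difference in performance between strata, which the article does not document.

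It is also fair to say that a condensed article may leave weighting and stratum-specific estimates to the full protocol or analysis plan. Their absence here is not the complaint. The sampling scheme and the basis for N are both stated, and they do not fit together.

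Part of the problem is already contained. Likelihood ratios are planned, and Aim 3 is limited to low-risk newborns with prevalence as a varied input. However, Aim 3 does not say which stratum supplies its sensitivity and specificity.

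Finally, 1% is the article's figure for CHD, whereas the working definition of SHD is broader. Fixing predictive values at exactly 1% would therefore not be clearly right either.

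**Conclusion.** The concern holds in conditional form. Block-stratified enrolment conflicts with a consecutive cohort sized at 1% prevalence unless strata fill at natural frequency, and the article does not say that they do. With any enrichment, N = 19/0.01 no longer describes the cohort, and raw PPV and NPV reflect the block ratio.

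The size cannot be determined without a ratio. Under the assumed mixes above, PPV runs from 16% to 76% against 8.8% at 1% prevalence, with the same sensitivity and specificity throughout. The effect on pooled sensitivity, specificity and C-statistic depends further on performance differing by stratum. The effect on net classification improvement follows in direction from the definition of the high-risk group, but its size depends on how many enter by an abnormal screen.

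**What to change.** 1. **Reconcile Patient enrolment, the Validation phase and the Statistic plan.** State whether strata fill at natural frequency or at a fixed ratio, how many newborns each stratum will have, and which stratum the 1% and the 19–20 cases refer to.
2. **If enriched, report by stratum.** Give sensitivity, specificity and net classification improvement separately for high-risk and low-risk newborns.
3. **Keep a log of eligible newborns per stratum from the first enrolment,** so that any pooled estimate can be weighted by the inverse of the stratum's sampling fraction. Such a log is hard to rebuild reliably afterwards.
4. **Do not present raw cohort PPV and NPV as screening values.** Compute them at a stated SHD prevalence for the target population, showing 1% and a range around it.

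The cost is small: revised wording, a screening log, and wider intervals for weighted estimates. If the strata do fill at natural frequency, one sentence saying so resolves the conflict.

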#### Validation phase

Study population will include newborns without previous cardiovascular examination and unknown cardiovascular status. Pre-test probability for SHD will be defined: high-risk newborn for structural cardiovascular abnormalities vs. neonates at low-risk (general population risk level). High-risk sub-group will include newborns with existing foetal ultrasound suggesting cardiovascular abnormalities and those with clinical indication for paediatric cardiology evaluation (abnormal neonatal screening, signs/symptoms). Low-risk sub-group (approaching patient level prevalence for structural cardiovascular abnormalities) will include consecutive neonates specifically enrolled for such research aim and without any indication for cardiovascular examination.

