**Figure 1 ztag103-F1:**
[figure not shown]
Diagram of validation phase. Each newborn with blinded cardiovascular status will undergo clinical screening as indicated by current practice and regulations and digital screening using the DI_SOUND algorithm. Gold standard evaluation will be comprehensive echocardiography. Pertinent diagnostics are reported at the bottom.

Cost-effectiveness validation (Aim 3)

Aim 3 will evaluate the potential impact of digital screening on healthcare utilization and costs compared with current standard clinical screening. The target population will consist of newborns at low risk for SHD, with no prior indication for cardiovascular examination, in order to approximate the prevalence of undiagnosed cardiovascular abnormalities in the general newborn population.

For the purpose of this analysis, outcomes will be explicitly defined as follows:

Prevented unnecessary examinations: cases in which (healthy) newborns with a positive result at standard clinical screening but a negative result at digital screening are subsequently confirmed to be free of SHD (i.e. false positives avoided by digital screening).Missed necessary examinations: cases in which newborns (with SHD) with a positive result at standard clinical screening but a negative result at digital screening are subsequently diagnosed with SHD (i.e. false negatives introduced by digital screening).

A decision-analytic modelling framework will be developed to compare digital screening with standard clinical practice. Model inputs will include estimates of SHD prevalence, test performance characteristics (sensitivity and specificity of both screening strategies), and downstream diagnostic pathways. Cost estimates will be derived from national diagnosis-related group reimbursement schedules to reflect healthcare system expenditures associated with confirmatory examinations and missed diagnoses.

To account for parameter uncertainty and variability, a probabilistic sensitivity analysis will be conducted using Monte Carlo simulation. This approach will allow repeated sampling from predefined distributions of key parameters (e.g. prevalence, sensitivity, specificity, and costs) to generate distributions of expected costs and outcomes for each screening strategy. The primary outcome will be the incremental cost-effectiveness of digital screening compared with standard clinical screening, expressed in terms of cost per unnecessary examination avoided and cost per missed SHD case.

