## Discussion

The DI_SOUND study is designed to develop and validate a digital classifier of neonatal cardiac sounds with the aim of improving the efficiency and effectiveness of screening for SHD in newborns. Current neonatal cardiovascular screening strategies rely on pulse oximetry (pre- and post-ductal oxygen saturation) combined with physical examination prior to discharge.^12–16^ While this approach has improved early detection of critical congenital heart disease, its diagnostic performance remains suboptimal, particularly in terms of sensitivity and operator dependency.^16^

Cardiovascular auscultation, historically a cornerstone of neonatal assessment, is inherently subjective and dependent on clinician experience.^14^ Several contemporary factors further limit its effectiveness. First, increasing prenatal detection of SHD has led to centralization of care, reducing exposure of general paediatric trainees and frontline providers to pathological cardiac findings, thereby potentially diminishing auscultatory proficiency.^35^ Second, early postnatal discharge (typically within 48–72 h) may occur before the full haemodynamic expression of certain defects, particularly those involving post-tricuspid shunts, due to persistently elevated pulmonary vascular resistance during transitional circulation. Third, the growing reliance on advanced diagnostic technologies may paradoxically reduce emphasis on meticulous physical examination skills.^35^ Collectively, these factors contribute to the persistence of false-negative screening results, which carry significant clinical risk.

Conversely, current screening strategies are also limited by suboptimal specificity, leading to a considerable number of false-positive cases. This results in unnecessary cardiology referrals, increased healthcare utilization, prolonged hospitalization, and heightened parental anxiety. Therefore, there is a clear unmet need for tools that can enhance both sensitivity and specificity while remaining accessible and scalable.

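### As written, Aim 2 sets a recording and echo at day 7 or later against what appears to be the pre-discharge clinical screen, so the comparison mixes the classifier with age

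*Protocol article*

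**What the plan says.** All references are to the Protocol article.

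- **Digital test and reference.** Validation phase, under Study procedure: "Age at recording and echocardiographic evaluation will be planned not before 7 days of post-natal life". The stated reason is that circulatory transition should be complete in healthy newborns. The inclusion criteria cap age at under 30 days.
- **Comparator.** The same section says "Clinical screening will be performed as mandated by the Italian law", and the Figure 1 legend describes "clinical screening as indicated by current practice and regulations". Neither gives an age.
- **Current practice.** The Discussion says that current strategies "rely on pulse oximetry (pre- and post-ductal oxygen saturation) combined with physical examination prior to discharge" and that "early postnatal discharge (typically within 48–72 h) may occur before the full haemodynamic expression of certain defects". It closes that list of limitations with the statement that "these factors contribute to the persistence of false-negative screening results".
- **Enrolment.** Patient enrolment: "For the validation phase consecutive newborns will be enrolled at the time of discharge from Ob/Gyn unit".
- **Risk stratum.** Validation phase, under Study population: the high-risk group includes "those with clinical indication for paediatric cardiology evaluation (abnormal neonatal screening, signs/symptoms").
- **Use of the results.** Under Statistic plan, net classification improvement over standard-of-care screening is the main Aim 2 analysis, scored within patient against the echo. Aim 3 takes the sensitivity and specificity of both strategies as model inputs.

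**The concern.** If the comparator is the routine screen, the two tests see the same newborn in different circulatory states, and the only reference examination is timed to one of them. A defect that becomes detectable between discharge and the later visit counts as a clinical miss and may count as a digital hit, whatever the quality of the classifier. The headline of Aim 2 would then be partly a statement about waiting, and the same numbers would pass into the Aim 3 model.

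Derivation recordings follow the same day-7 rule. On this reading the classifier is neither trained nor tested at the age of the screen it is compared with, so the result could not speak to use at discharge.

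The Limitation section discusses several reasons why the two methods may differ, but not the age gap. The article also schedules no clinical examination at the age of the recording.

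**Working it through.** **1. Ages, set side by side.**

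| Test | Age | Basis |
|---|---|---|
| Clinical screen | before discharge, typically 48–72 h | inferred: mandated screen (Validation phase), current practice (Figure 1 legend), before discharge at 48–72 h (Discussion), enrolment at discharge (Patient enrolment) |
| Digital recording | day 7 to 29 | stated |
| Reference echo | day 7 to 29 | stated |

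The smallest gap is 7 − 3 = 4 days and the largest about 29 − 2 = 27 days. The age ranges do not overlap. On this reading no adjustment for age in the analysis can separate age from method, because every clinical result is early and every digital result late.

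**2. Direction.** For sensitivity the Discussion supplies it: discharge may come before some defects are fully expressed, above all post-tricuspid shunts, and this contributes to false negatives. For specificity the article supplies no clear direction. The day-7 rule implies that healthy newborns are still in transition earlier, but Table 2 classes a physiologic murmur as a negative screen.

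**3. How the gap enters the estimate.** For two binary tests, net classification improvement = (Se digital − Se clinical) + (Sp digital − Sp clinical). Suppose both methods are equal at equal age, and early timing lowers clinical sensitivity by *a* and clinical specificity by *b*. The expected improvement is then *a* + *b*. With both tests at one age it would be 0.

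**4. Illustration.** The documents give neither *a* nor *b*; the values below are assumptions. The scale comes from the Statistic plan: 1,900 × 0.01 = 19 cases and 1,900 − 19 = 1,881 healthy newborns.

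- *a* = 0.05: 19 × 0.05 ≈ 1 extra clinical miss. *a* = 0.20: 19 × 0.20 ≈ 4.
- *b* = ±0.02: 1,881 × 0.02 ≈ 38 clinical false positives, more or fewer.
- *b* = 0: apparent improvement 0.05 to 0.20.
- *b* between −0.02 and +0.02: from 0.05 − 0.02 = 0.03 to 0.20 + 0.02 = 0.22.

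The counts use 1% prevalence. The validation cohort is block-stratified by risk, so the actual case count may differ. The sum *a* + *b* does not depend on it.

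**5. Is the comparator the routine screen? A conflict inside the article.** An abnormal neonatal screen places a newborn in the high-risk group. Aim 3 is confined to low-risk newborns with no prior indication for cardiac examination, yet both of its defined outcomes require a positive clinical screen.

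- If the comparator is the routine screen, positives leave the Aim 3 population and almost nothing remains to count.
- If the comparator is a separate, later examination, Aim 3 works, but the article nowhere says that such an examination takes place.

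The two sections need reconciling under either reading.

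**The case against.** The case against has real weight.

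- **The age of the screen is inferred.** The Validation phase places consent first and then describes the clinical screen in the future tense, which can be read as a study procedure after enrolment. The 48–72 h figure is background on discharge, not a protocol setting. The full study protocol, in supplementary material not shown here, may hold a visit schedule. This stands: a reader might take the pre-discharge age as fact, and the article does not state it. The Aim 3 conflict above even points the other way.
- **Large spurious gains are not shown.** A reader might assume 85% sensitivity and 5%, 15% or 30% of lesions not yet audible at discharge, and infer gains of 0.85 × 0.05, 0.15 or 0.30, about 4, 13 or 26 points. Those inputs are not in the article. The sum also ignores that the clinical screen includes oximetry and femoral pulses, so an inaudible lesion is not necessarily a miss.
- **Prevented examinations cannot be counted this way.** A reader might also infer that transient murmurs in 2–5% of healthy newborns yield 1,881 × 0.02 to 0.05 × 0.95, about 36 to 89 examinations spuriously prevented. On the pre-discharge reading those newborns are high-risk and outside Aim 3, and a physiologic murmur is a negative screen under Table 2.
- **The bias need not favour the digital tool throughout.** A critical defect found before day 7 may be diagnosed or treated before any recording. The Introduction's remark on weaker oximetry concerns the first 24 h, so it does not bear on 48–72 h against day 7.
- **Standard care is a legitimate comparator.** The day-7 rule has a stated reason, and the Discussion calls the tool complementary. This also stands, provided the comparison is labelled as one of strategies at different ages. The article does not do so: it presents the gain as that of the classifier.

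**Conclusion.** The point holds in a limited form. Read as a whole, the article sets a digital test and its only reference at day 7 or later against what appears to be the routine pre-discharge screen, and it says itself that early timing contributes to missed disease. As written, the Aim 2 improvement and the Aim 3 inputs therefore mix the classifier's effect with that of age, probably in the classifier's favour on sensitivity.

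The documents do not establish the exact age of the clinical screen, the direction for specificity, a uniform direction across lesions, or any size. The range of 0.03 to 0.22 rests wholly on the assumed 5 to 20 points of sensitivity and ±2 points of specificity, with the two screens assumed equal at equal age. If the sponsor intends a clinical examination at the recording visit, the age effect disappears, but the article must then say so. The matter should be settled before validation enrolment, because on the pre-discharge reading it cannot be repaired in the analysis.

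**What to change.** 1. State the planned age at the clinical screen, the recording and the echo, and record the actual age at each.
2. If the ages differ, define Aims 2 and 3 as digital screening at 7 days or later versus clinical screening before discharge. Do not attribute the difference to the classifier, and do not extend it to discharge screening.
3. Preferably add a same-age comparison. Either record the Table 2 findings at the existing day-7-or-later visit, blind to recording and echo, or take a 15 s research recording at the discharge enrolment contact. Keep the standard-of-care screen as a separately labelled comparison.
4. Reconcile the high-risk definition (abnormal neonatal screening) with the Aim 3 outcomes, which count positive clinical screens among low-risk newborns.

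Items 1, 2 and 4 are mainly wording, plus the recording of ages. Item 3 costs a few minutes at a contact that already takes place. The downside is that the apparent gain over clinical screening will probably be smaller.
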